### Sample size

3.2

In this study, the PFS2/PFS1 ratio will be used as primary outcome measure, in which the correlation of two consecutive lines of treatment allows the patient to serve as her own control and compensates for heterogeneity in patient characteristics and tumour histology. Two prior prospective studies used the PFS2/PFS1 ratio to measure treatment response on targeted therapies based on molecular profiling in patients with advanced cancers [17,46]. Both studies deemed a PFS2/PFS1 ratio ≥ 1.3 to clinically beneficial. Their null hypothesis stated that ≤ 15 % of the patient population would have a PFS2/PFS1 ratio of 1.3 on standard therapy. In order to reject the null hypothesis, the authors assumed that the true proportion of patients with a PFS2/PFS1 ratio ≥ 1.3 in the studies would be equal to 30 % [46] and 24 % [17].

Based on these results, we calculated that 37 evaluable patients are required per treatment arm (total of 148 patients for treatment arm A, B, C and D) to reject the null hypothesis of an estimated 15 % of patients achieving PFS2/PFS1 ratio ≥1.3 on standard palliative therapy with 80 % power at a one-sided significance level of 0.10.

Per stepwise executed treatment arm, interim analyses will be performed after the inclusion of the first eight and 24 patients (Fig. 1) [30]. In case none of the first eight patients achieve PFS2/PFS1 ≥ 1.0, the treatment arm will be closed due to lack of efficacy. The treatment arm will be complemented by 16 additional patients if at least one of the first eight patients achieves PFS2/PFS1 ≥ 1.0. In case at least five of the enrolled 24 patients achieve PFS2/PFS1 ≥ 1.0, the treatment arm is considered a potentially successful treatment and may proceed with enrolment until 37 patients have been included. If four or less patients achieve PFS2/PFS1 ≥ 1.0, the treatment arm will be closed due to insufficient efficacy. For this monitoring rule, we choose the threshold of 1.0 to represent sufficient patient benefit to continue patient accrual. After closing a treatment arm, it is allowed to open a new treatment arm targeting the same STP with a new targeted drug, if this is deemed beneficial by the MTB.

Patients who withdraw from the study before start of matched targeted therapy will be replaced until a total of 37 patients are available for response measurements. If a patient withdraws from the study after the start of matched targeted therapy, the patient will not be replaced and will be included in the analysis.

Our research group investigated STP activity in previous cohorts of women with HGSC and LGSC [28,29,43]. Based on our observations in these studies, we anticipate the presence of an active ER, AR, PI3K or HH pathway in approximately 50 % of the patients included in the study. It is expected that approximately 10 % of the cases will result in biopsies with insufficient tumour percentages. Additionally, considering a drop-out rate of 10 % prior to the initiation of targeted therapy, we estimate that a total of 366 patients will need to undergo biopsy to achieve intended sample size for this study. We estimate to be able to recruit sufficient number of patients for study arm A, B, C and D in five years, in a total of six participating centres in the Netherlands.

### Plan of analysis

3.3

The proportion of patients who achieved a PFS2/PFS1 ratio ≥ 1.3 will be calculated from the total of patients that received matched targeted therapy. The primary endpoint will be tested by a one-sided exact test. Since histological subtype is a prognostic factor for PFS [36], subgroup analysis will be performed in case of adequate numbers.

Planned statistical analysis for the secondary outcome measures include the Kaplan-Meier survival curves tested with log-rank tests and Cox proportional hazard models for survival analysis. Furthermore, the predictive value of STP activity assay will be determined by correlations between STP activity scores and PFS2 using the Pearson or Spearman correlation coefficient. If patients undergo a voluntary second post-treatment biopsy, change in STP activity score will be calculated for each respective STP compared to the STP scores from the pre-treatment biopsy.

Using the appropriate algorithms, the side effects and health-related quality of life questionnaires will be analysed and compared accordingly between the group of patients that received matched targeted therapy and patients that received standard therapy. Together with the PFS, these results will be used in a quality adjusted life year calculation in order to calculate the cost-effectiveness and cost-utility ratios of matched targeted therapy. In addition, subgroup analysis per treatment arm will be conducted.

Descriptive statistics will be used to describe patient characteristics. Categorical variables will be expressed as a number with the percentage of the total study group. The chi-squared test or Fisher's exact test will be used to analyse associations between categorical variables. Continuous variables will be presented as mean with standard deviation or as median with interquartile range, whenever appropriate. A *t*-test or Mann-Whitney *U* test will be used to analyse associations between continuous variables.

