### Outcome measures

3.1

The primary objective of this study is the progression-free survival (PFS) ratio (PFS2/PFS1 ratio) defined by the PFS on matched targeted therapy by STP activity assay (PFS2) in comparison to the PFS recorded on the therapy administered immediately prior to enrolment (PFS1) [31].

Secondary outcome measures include.•Proportion of patients with an actionable active STP for which targeted therapy is recommended in relation to the number of patients who underwent a biopsy.•Proportion of patients who receive matched targeted therapy in relation to the number of patients included in each study arm.•Best overall response defined by RECIST 1.1 based on radiological imaging [31].•One-year survival defined as the time from start matched targeted therapy till death or the end of the one-year follow-up period.•Overall survival defined as the time from start matched targeted therapy till death.•Predictive value of STP activity assay results (and if available, immunohistochemical biomarker analysis and DNA/RNA sequencing results) on matched targeted therapy response.•Change in STP activity score after disease progression (if available) compared to STP activity score before start of matched targeted therapy.•Side effects according to PRO-CTCAE™.•Health-related quality of life scored using standardized questionnaires from the EORTC (QLQ-C30 and QLQ-OV28) [44].•Cost-effectiveness will be calculated with health state utilities assessed in the standardized EuroQol 5D (EQ-5D-5L) questionnaire [45].

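### The assay's predictive value is to be judged by Pearson or Spearman correlation with PFS2, a time that can be right-censored and that these coefficients cannot handle

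*Protocol article*

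**What the plan says.** Outcome measures (3.1) lists as a secondary outcome: "Predictive value of STP activity assay results (and if available, immunohistochemical biomarker analysis and DNA/RNA sequencing results) on matched targeted therapy response". Plan of analysis (3.3) assigns its method: it will be "determined by correlations between STP activity scores and PFS2 using the Pearson or Spearman correlation coefficient".

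The sentence just before that one names "Kaplan-Meier survival curves tested with log-rank tests and Cox proportional hazard models for survival analysis". Methods that respect censoring are therefore in the plan, but the assay question is given a different one.

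Three other places bear on the point:
- Sample size (3.2) says of a patient who withdraws after starting matched therapy that "the patient will not be replaced and will be included in the analysis". Ethics and dissemination (3.4) lets participants withdraw at any time for any reason.
- Outcome measures defines the comparator for the primary ratio as "the PFS recorded on the therapy administered immediately prior to enrolment (PFS1"), so PFS1 is on record for treated patients.
- Sample size justifies the ratio because it "allows the patient to serve as her own control and compensates for heterogeneity in patient characteristics and tumour histology". The correlation uses PFS2 without PFS1.

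**The concern.** A correlation coefficient needs a complete value for every patient. Faced with a censored PFS2, the analyst must either enter the follow-up time as if progression had occurred then, or drop the patient. The first understates the censored times, and at data cut-off these include the longest progression-free times. The second selects patients by outcome.

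At stake is a listed secondary outcome that feeds directly into the article's closing statement about the clinical applicability of STP activity. A weakened coefficient could make a useful score look uninformative. If patients with high or low scores leave at different rates, a coefficient could also suggest an association that is not there. Because the method is stated outright, an analysis plan that follows the article would carry the problem forward.

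**Working it through.** **The plan's own figure.** The article gives no sample size, power or censoring rate for this analysis. The only usable input is "37 evaluable patients are required per treatment arm (total of 148 patients for treatment arm A, B, C and D"), planned "with 80 % power at a one-sided significance level of 0.10". That number reproduces. With an exact binomial test, null 15% and alternative 30%, the smallest n is 37 with success at 9 or more: P(X ≥ 9 | 37, 0.15) = 0.0924 and P(X ≥ 9 | 37, 0.30) = 0.824. Four arms give 4 × 37 = 148. Only n is carried forward.

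**Model (assumed, not in the article).** Score x is standard normal. PFS2 time T is exponential with rate λ·exp(βx), where β = ln 0.65 = −0.431 per SD. Censoring time C is independent of x and T. The observed time is min(T, C). The coefficients treat min(T, C) as T. Cox also uses the event indicator. Tests are two-sided at 5%, n = 37.

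| Censored | Mean Pearson r | Pearson power | Spearman power | Cox power | Cox − Pearson | Cox − Spearman |
|---|---|---|---|---|---|---|
| 0% | 0.37 | 65% | 55% | 66% | 1 | 11 |
| 10% | 0.34 | 56% | 46% | 62% | 6 | 16 |
| 20% | 0.30 | 45% | 38% | 57% | 12 | 19 |
| 35% | 0.24 | 32% | 28% | 47% | 15 | 19 |

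The mean r falls by 1 − 0.30/0.37 = 19% at 20% censoring and by 1 − 0.24/0.37 = 35% at 35%, while the Cox log hazard ratio stays stable. Cox also loses power, because there are fewer events. The last two columns (percentage points) show the cost of the method. A separate run of the same model with 1,500 replicates gave, at 0/20/35%, Pearson 63/43/31%, Spearman 52/37/25% and Cox 65/56/47%. The two runs agree within 3 points.

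**How much censoring is plausible?** With a 16-week median PFS2 (assumed) and censoring only at data cut-off:
- 5-year accrual, one-year minimum follow-up: 2% censored; Pearson/Spearman/Cox power 62/52/65%.
- 5-year accrual, 12-week minimum follow-up: 6% censored; 57/50/62%.
- 2-year accrual per arm, 12-week minimum follow-up: 15% censored; 52/47/60%.

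The Pearson–Cox gap is then 3, 5 and 8 points.

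**Censoring that depends on the score.** With n = 37, no true effect and 30% censoring linked to the score, mean Pearson r was about −0.23 or +0.24, depending on which patients leave early. The false-positive rate was about 27–28% for Pearson and Spearman, against 5–6% for Cox. At 20% censoring it was about 14–17%, against about 5%.

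**Two possible repairs** (separate simulation, hazard ratio 0.61 per SD, n = 37 unless stated):
- Dropping censored patients does not help: at 30% censoring, Spearman power is 29%, against 40% with all patients and 62% for Cox.
- Pooling arms does not help either: at n = 148, hazard ratio 0.78 per SD and 30% censoring, power is 54% (Pearson), 42% (Spearman) and 71% (Cox).

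**PFS1.** If PFS1 and PFS2 share an unmeasured patient effect, adding log PFS1 to the Cox model gains about 2–5 points of power.

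**The case against.** The best defence is that censoring may be slight. Accrual is planned over five years, and if PFS2 is short most patients will have progressed by cut-off. Reaching 20–35% would need substantial withdrawal without progression, for which the article gives no figure. The sentence on non-replacement is also weak evidence by itself, since End of treatment (2.11) uses withdrawal to describe patients who have progressed. This stands as a limit on size. It does not make the method right: withdrawal for any reason is allowed, cut-off censoring is possible, and the rate is unknown in advance.

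A reader might infer more than the text supports:
- **That the bias is always toward zero.** That holds only when censoring is independent of the score.
- **That censoring causes the whole power gap.** Spearman already trails Cox by 11 points with none, because the simulated data follow proportional hazards, which suits Cox.
- **That scores from different pathways are correlated in one pool on mixed scales.** Pooling is nowhere stated. The Plan of analysis announces subgroup analysis per arm, and the assay section presents each pathway with its own cut-off.
- **That adjusting for PFS1 would separate prediction from prognosis.** Every patient in this analysis receives matched therapy, so no model within the cohort can fully do so.
- **That the trial's main conclusion is at risk.** The primary endpoint is the PFS2/PFS1 ratio. This is one of ten secondary outcomes, with no stated error rate or decision rule.

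**Conclusion.** The point holds in limited form. The article fixes a method that cannot use censored times for an outcome that can be censored, although Cox models are named one sentence earlier. The harm ranges from negligible for Pearson with no censoring (65% against 66% power), through about 3–8 points with cut-off censoring alone, to 12–15 points for Pearson and 19 for Spearman at 20–35% censoring. If censoring depends on the score, the larger danger is a misleading association in either direction.

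These sizes rest on an assumed hazard ratio of 0.65 per SD, exponential times, 37 patients and assumed censoring rates. The direction of the argument does not rest on them. Cox has its own condition: censoring must be unrelated to imminent progression, given the score. The point is worth correcting because the correction is nearly free. It does not touch the primary test, the stopping rules or the sample size.

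**What to change.** Replace the correlation sentence in the Plan of analysis. For the predictive value of the assay, fit a Cox model of PFS2 with the matched pathway's score as a continuous covariate, per arm, or stratified by arm if arms are pooled. State the rule for censoring PFS2. Report the hazard ratio with its confidence interval and a censoring-adjusted concordance index. Keep Spearman, if wanted, as a description only.

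Adjustment for log PFS1 is an optional addition. It reduces confounding by prognosis without removing it, and should be described that way.

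The cost is a change of wording. Score, PFS1 and PFS2 are already recorded, and no extra patients or visits are needed.

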### Ethics and dissemination

3.4

The study will be conducted according to the principles of the Declaration of Helsinki (amended by the 68th WMA General Assembly, Chicago, United States, October 2017). All researchers involved in the study will follow the Dutch Medical Research Involving Human Subjects Act and ‘Code Goed Gebruik’ (Federa 2002, amended in 2011). Ethical approval for the study has been obtained from the Medical research Ethics Committees United (MEC-U, study number R21.033) and Central Committee on Human Research (CCMO, study number NL77022.100.21). The study has been registered with the European Union Drug Regulating Authorities Clinical Trials (EudraCT) database under reference number NL2020-005091-36 and with ClinicalTrials.gov under reference number NCT03458221.

All participants will be informed on the purpose, procedure, duration and possible risks and benefits of the study. Participants need to provide written informed consent prior to study inclusion and, in case a matched targeted drug is available and recommended, prior to the start of therapy. Participants can withdraw consent to participate at any time for any reason and without any consequences.

All data will be handled strictly confidential and will be collected using an eCRF in the secured database Research Manager (https://my-researchmanager.com). Data and tumour tissues will be coded with a random study number and will be stored for at least 15 years after the end of the study.

Study results of individual cohorts or pooled data will be offered to international peer-reviewed journals for publication and presented at conferences. Publication will not disclose the identity of the participants.

## Conclusion

4

This is the first study to evaluate the clinical implementation of *phenotype*-guided targeted therapy based on STP activity in tumour tissue of patients with recurrent ovarian cancer. Patients are treated with existing targeted drugs with tolerable toxicity profiles to investigate whether these drugs have therapeutic value beyond their approved indications. The unique study design allows for simultaneous screening for several promising treatment strategies and rapid incorporation of new cohorts based on other (off-label) targeted drugs or STPs. Intra-individual comparison of treatment response through the PFS ratio will limit confounders such as tumour histology. The results of this study will show the clinical applicability of STP activity to match recurrent ovarian cancer patients to targeted therapies.

